### Study parameters

#### Baseline data

Patients will all have a full medical history taken and clinical examination as part of their usual care. The following will be recorded:WeightHeightBlood pressureHeart rateECGGenderEthnicityDate of birthDiabetes mellitusHypercholesterolaemiaHypertensionPrevious myocardial infarctionPrevious coronary revascularisationPrevious strokeAtrial fibrillationPeripheral arterial diseaseSmoking historyNYHA classMedication at time of consent (aspirin, clopidogrel, beta-blocker, calcium-channel antagonist, nitrates, cholesterol-lowering agent, ACE inhibitor/A2 receptor antagonist, insulin, metformin, sulphonylurea, or warfarin)Serum creatinine and troponin.

### Perioperative troponin

This will be assessed by measuring serum high-sensitivity troponin I pre-operatively and at 24, 48 and 72 hours post-operatively (four samples per patient). The samples will be analysed in the local laboratory at each site, using local protocols.

### Perioperative 12-lead electrocardiography

A 12-lead ECG is performed routinely as part of the pre-operative assessment for major vascular surgery. This will be used as the trial baseline ECG. Every patient will undergo a second 12-lead ECG on the second post-operative day. The pre- and post-operative ECGs together with the serum troponin levels will be reviewed by the trial cardiologists to determine whether a perioperative silent myocardial infarction has occurred. The reviewing cardiologists will be blinded to trial allocation.

### Length of hospital/intensive therapy unit stay

The duration of hospital stay and intensive therapy unit (ITU) stay have a major impact on health service resource utilisation, and are factors that can be influenced by surgery.

### Acute kidney injury score

The acute kidney injury (AKI) score will be calculated over the first three perioperative days. Creatinine will be measured daily as part of routine care. Urine volumes will be calculated from the fluid balance charts maintained as part of usual care.

### Perioperative data

On the morning of surgery, the patient will be randomised to either the RIPC or control arm using a web-based system. The following information on surgery will be recorded for all patients: anaesthetic induction agents, anaesthetic maintenance, duration of anaesthesia, type of surgery, blood loss, maximum intra-operative heart rate, minimum intra-operative systolic blood pressure. For open AAA patients, the following additional data will be recorded: infra-renal or suprarenal aortic clamp, cross-clamp time, and mannitol use. For carotid endarterectomy patients, shunt use and patch use will be recorded. For endovascular aneurysm repair patients, screening time and total contrast dose will be recorded.

### Data at discharge

At discharge, duration of hospital stay and ITU stay will be recorded.

### Data at 1 year

General practitioners will be contacted 1 year following randomisation to ascertain whether participants have died or suffered myocardial infarction or cerebrovascular accident. The national Hospital In-Patient Episode (HIPE) database will be interrogated for hospital admissions and patient status in the year since surgery.

### Trial outcome measures

#### Primary efficacy endpoint

The trial is intended to pragmatically evaluate the potential of RIPC to improve clinical outcomes among patients undergoing major vascular surgery in routine clinical practice. For the pilot trial, a surrogate marker of efficacy will be used, namely serum troponin I levels. The primary efficacy outcome will be a comparison of the proportion of patients in each arm of the trial who develop a raised serum troponin level in the first three post-operative days. For patients with a baseline troponin level within the normal range, this outcome will be considered positive when any subsequent troponin level at 24, 48 or 72 hours post-operatively is above the upper limit of normal. For patients with a baseline troponin level that is above the normal range, this outcome will be considered positive when any subsequent troponin level at 24, 48 or 72 hours post-operatively is above the baseline value. This is a dichotomous outcome for individual patients.

#### Primary safety endpoint

The intervention under investigation carries a theoretical risk of causing acute upper limb ischaemia or an upper limb deep vein thrombosis. Such an event has not been reported by any of the phase 1 and 2 trials of RIPC in cardiac patients. In addition, there is a theoretical risk of minor adverse events such as upper limb bruising. The primary safety endpoint will again be a composite of major life- or limb-threatening adverse events that could be attributed to the preconditioning stimulus. The components are:Acute upper limb ischaemiaAcute upper limb deep vein thrombosis

The components of the primary safety endpoint are defined as follows:Acute upper limb ischaemia, which is defined as the development of ischaemia in the arm used for the preconditioning stimulus requiring systemic anti-coagulation, radiological intervention or surgical intervention; andAcute upper limb deep vein thrombosis, which is defined as the development of thrombus within the subclavian, axillary or brachial vein confirmed in duplex ultrasound and in the same arm as used for the RIPC stimulus.

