### Intervention

The intervention being tested is a simple intervention that can be undertaken using existing equipment. Immediately before the start of the operation, patients randomised to the RIPC arm will have a standard, CE-approved tourniquet cuff placed around one upper limb. It will then be inflated to a pressure of 200 mmHg for 5 minutes. For patients with a systolic blood pressure >185 mmHg, the cuff will be inflated to at least 15 mmHg above the patient’s systolic blood pressure. The cuff will then be deflated and the arm allowed to reperfuse for 5 minutes. This will be repeated so that each patient receives a total of four ischaemia-reperfusion cycles. There is no sham intervention for those in the control arm.

Previous trials of RIPC in cardiac surgery and percutaneous coronary interventions have generally used the arm as the source of the RIPC stimulus. Four previous trials of RIPC in major vascular surgery (Table 1) used the patients’ legs to generate the stimulus. In these trials, four patients in the RIPC arm developed post-operative critical lower limb ischaemia requiring intervention. The presence of known peripheral arterial disease also precluded the enrolment of about 20% of otherwise eligible patients. Given the success of upper limb RIPC in the cardiac and percutaneous coronary intervention (PCI) trials, the upper limb has been selected as the source for the RIPC stimulus in Preconditioning SAVES. In common with the ERICCA trialists [27], four cycles has been chosen in order to maximise the RIPC stimulus obtained and counteract three potential confounding issues: (i) the lower skeletal muscle bulk in the arm compared to the leg, (ii) the potential resistance to RIPC in aging and diabetic patients and (iii) the effect of variable volatile anaesthetic use.

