**Table 2 Tab2:** **Definitions of other post-operative complications**

Respiratory failure	Unplanned initiation of assisted ventilation (CPAP or IPPV)
Transient ischaemic attack	New onset neurological deficit with lateralising signs, which resolves within 24 hours without evidence of cerebral bleeding or infarction on imaging and confirmed by a stroke physician or neurologist
Vascular graft occlusion	Occlusion of prosthetic or vein graft confirmed by imaging within 30 days of surgery
Wound infection	Erythema, purulent discharge, pyrexia, positive pathogenic organism on culture
Chest infection	Cough, dirty sputum, pyrexia, positive sputum culture +/−pathogenic organism on sputum culture
Urine infection	Pyrexia, leucocytosis, pathogenic organism on urine culture
Abdominal infection	Intra-abdominal abscess formation confirmed on CT scan or at laparotomy
Other sepsis	Sepsis due to any cause other than those listed above for example, line infection
Prolonged ileus	Absence of bowel function requiring the initiation of nutritional support
Pulmonary embolus	Confirmed radiologically or at autopsy
Deep vein thrombosis	Confirmed radiologically or at autopsy
Limb ischaemia	Compromised circulation in a limb requiring a revascularisation procedure within 30 days of surgery
Major limb amputation	Amputation of a limb due to unsalvageable critical ischaemia within 30 days of surgery
Renal infarction	New renal infarction on post-operative imaging
Renal impairment	Post-operative ≥20% increase in serum creatinine from pre-operative baseline

CPAP – continuous positive airway pressure; IPPV – intermittent positive pressure ventilation.

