### Final analysis

Once the trial has closed, a final analysis of the data will be conducted by [name], the trial biostatistician. The trial arms will be labelled A and B, to maintain blinding. Baseline characteristics will be compared between the trial arms to evaluate the efficacy of randomisation. The proportions of patients with troponin positive events, components of the composite clinical outcome, primary safety endpoints, troponin levels, unplanned critical care admission and other post-operative complications will be compared between the trial arms. Hospital stay and intensive care unit stay will also be compared between the two trial arms. One-year survival and cardiac- and cerebral-event free survival will be compared. These results will all be presented in the final trial report.

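### The primary safety endpoint can occur only in a cuffed arm, so controls score zero by definition and the planned between-arm comparison cannot show excess harm

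*Protocol article*

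**What the plan says.** Under Primary safety endpoint, the article sets out to capture "a composite of major life- or limb-threatening adverse events that could be attributed to the preconditioning stimulus". It then lists two components. Acute upper limb ischaemia is "the development of ischaemia in the arm used for the preconditioning stimulus requiring systemic anti-coagulation, radiological intervention or surgical intervention". Acute upper limb deep vein thrombosis is thrombus in one of three named veins, "confirmed in duplex ultrasound and in the same arm as used for the RIPC stimulus".

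The Intervention section states: "There is no sham intervention for those in the control arm". The Final analysis section lists the endpoint among the items to be tested by group: "primary safety endpoints, troponin levels, unplanned critical care admission and other post-operative complications will be compared between the trial arms". Arms are labelled A and B to keep the statisticians blind (Statistical analysis plan; Final analysis). Those who assess outcomes other than silent infarction are also to be blind to allocation (Evaluation of other outcomes).

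The Intervention section also allows cycles of leg ischaemia to be added after an interim analysis at 200 patients, with a new ankle-brachial exclusion. It reports that in the earlier leg-stimulus trials "four patients in the RIPC arm developed post-operative critical lower limb ischaemia requiring intervention". Table 2 holds a separate item, limb ischaemia, defined as "Compromised circulation in a limb requiring a revascularisation procedure within 30 days of surgery".

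**The concern.** A between-group comparison needs an outcome that either group can have. Here the definition contains the exposure. A control patient with an ischaemic or thrombosed arm, for example after cannulation, is not counted, while a RIPC patient with the same event in the cuffed arm is. The comparison would therefore show the cuff as harmful or neutral and could never show it as safer. Any excess would mix cuff harm with events that would have happened anyway.

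Two further consequences follow. An assessor who must decide whether the affected arm was the cuffed one has to know that the patient was cuffed, and on which side. And a statistician who sees one safety event under label A or B knows which label is RIPC.

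A secondary concern is that the stimulus may be extended to the leg, while the safety endpoint has no lower limb component and no change to it is foreseen.

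**Working it through.** The article gives no figure for the safety endpoint, so there is none to reproduce. The check is mainly one of definition.

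**Inputs.** 200 patients per arm (Sample size); both components confined to the stimulated arm (Primary safety endpoint); no cuff and no sham in controls (Study design; Intervention); between-arm comparison (Final analysis).

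**Step 1: the control count.** An event counts only if it lies in a limb that received the stimulus. No control limb did. The control result is 0/200 before any data are seen.

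**Step 2: what the difference estimates.** Let b be the risk of a qualifying event in the cuffed arm without any cuff effect, and d the excess caused by the cuff. For small risks these add.

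- As written: RIPC b + d, control 0, difference b + d.
- With either upper limb counted in both groups, and B the background risk for either limb: RIPC B + d, control B, difference d.

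Only the second isolates the cuff effect.

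**Step 3: what a test would do.** Two-sided Fisher exact test against 0/200: 5/200 gives p = 0.061 and 6/200 gives p = 0.030. These p-values are the same whether the events come from the cuff or from background, because the control cell cannot move. This shows the structure and is not a forecast: 6/200 is 3% in the cuffed arm alone, and the article says no such event was reported in the phase 1 and 2 cardiac trials.

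**Step 4: what the current definition can support.** It can support a one-group rate. With 0 events in 200 RIPC patients, the one-sided 95% upper limit is 1 − 0.05^(1/200) = 0.0149, about 1.5%. That is useful, but it is not a comparison.

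**Step 5: blinding.** Every qualifying event belongs to RIPC, so the first one identifies the label. The labels apply to all analyses, so this could include the interim analysis if safety is tabulated there, which the article does not say.

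**Step 6: the leg, as a signal only.** The four leg-stimulus trials in Table 1 randomised 82 + 40 + 40 + 70 = 232. Assuming 1:1 allocation, 232/2 = 116 received RIPC, and 4/116 = 3.4% (Clopper-Pearson 95% CI 0.9% to 8.6%). The article gives neither the split nor a control count. Side by side: Primary safety endpoint counts upper limb ischaemia treated by anticoagulation alone, whereas the limb ischaemia item in Table 2 requires revascularisation. A leg event treated without revascularisation would thus meet neither definition.

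**The case against.** The strongest reply is that limb events are compared elsewhere. Table 2 has items for limb ischaemia, deep vein thrombosis and major limb amputation that are not restricted to a cuffed limb, and Final analysis compares these complications between arms. This stands in large part. A reader might infer that limb harm in controls goes unrecorded; it does not. What remains is that the endpoint named as primary for safety cannot support its stated comparison. Table 2 does not replace it, because it does not separate upper from lower limb and misses ischaemia treated without revascularisation.

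Site-specific attribution is also a legitimate choice for a local harm. That is true for a descriptive rate in RIPC patients, but the article commits to a comparison.

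On blinding, the primary efficacy outcome is a laboratory dichotomy, so a statistician who learns the label can do limited damage. That is fair, and the point is secondary.

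On the leg, a reader might infer that 3.4% implies three or four uncounted events per 100 leg-stimulated patients. The documents do not support that forecast. The clause may never be invoked. It operates through a protocol amendment, which could revise the endpoint. The added ankle-brachial exclusion may lower the rate. Because the interim analysis waits for 30-day follow-up and no recruitment pause is stated, fewer than 100 RIPC patients may be affected. With no control count, the four events do not show that the leg stimulus caused them.

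**Conclusion.** The concern holds for the upper limb endpoint and does not depend on any assumed rate. The definition, the untreated control group and the planned comparison cannot all stand: the control count is 0/200 by construction, and the difference estimates background plus cuff effect. The wording also conflicts with blinded outcome assessment and with the A/B labelling. Efficacy analysis and sample size are unaffected.

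The leg point holds only as a gap to reconcile between Intervention and Primary safety endpoint, and only matters if the leg stimulus is added. The figure of 4 in about 116 (3.4%, 95% CI 0.9% to 8.6%) rests on an assumed 1:1 split, has no control count, and is a signal and no more. Until such a change, Table 2 would record most lower limb events as secondary complications.

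**What to change.** 1. Define the primary safety endpoint as acute ischaemia or deep vein thrombosis of either upper limb, in both groups, keeping the existing severity and confirmation criteria.
2. Have the blinded assessor record the event and its side. Record cuff status and cuffed side separately, and link them afterwards.
3. Compare the either-limb endpoint between groups. Report cuffed-arm events in RIPC patients descriptively, with an exact confidence limit and outside the A/B-labelled tables.
4. Reconcile Intervention with Primary safety endpoint, so that if the leg stimulus is added, lower limb events enter the safety endpoint and are compared between groups among patients randomised after the change. State how ischaemia treated without revascularisation is then captured.

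The cost is endpoint wording and a case record form field for side and cuff status, settled before any results by arm are seen. The small downside is that some unrelated upper limb events will be counted in both groups. Adding lower limb events for every patient from the start is not recommended as a default: the trial enrols lower limb revascularisation patients, whose graft and disease events could swamp an endpoint meant for harm from the stimulus.

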### Secondary endpoints

Secondary endpoints are identified as follows:The proposed composite primary efficacy endpoint for a phase 3 trial (details below)A comparison of the area under the curve of serial troponin values between the two groupsDuration of post-operative hospital stay in days from the date of surgery until the date of discharge to the communityDuration of intensive care unit stay in days from the date of surgeryUnplanned critical care unit admission defined as any admission to a high dependency or intensive care unit, which was not booked in advance of the date of operationOther post-operative complications (Table 2)Acute kidney injury score in first three perioperative days (Table 3)Death within one year of surgery as determined by contacting the patient’s general practitionerMajor adverse cardiac or cerebral event (myocardial infarction, cardiac death, cerebrovascular accident) within 1 year of surgery as determined by contacting the patient’s general practitioner

**Table 2 Tab2:** **Definitions of other post-operative complications**

Respiratory failure	Unplanned initiation of assisted ventilation (CPAP or IPPV)
Transient ischaemic attack	New onset neurological deficit with lateralising signs, which resolves within 24 hours without evidence of cerebral bleeding or infarction on imaging and confirmed by a stroke physician or neurologist
Vascular graft occlusion	Occlusion of prosthetic or vein graft confirmed by imaging within 30 days of surgery
Wound infection	Erythema, purulent discharge, pyrexia, positive pathogenic organism on culture
Chest infection	Cough, dirty sputum, pyrexia, positive sputum culture +/−pathogenic organism on sputum culture
Urine infection	Pyrexia, leucocytosis, pathogenic organism on urine culture
Abdominal infection	Intra-abdominal abscess formation confirmed on CT scan or at laparotomy
Other sepsis	Sepsis due to any cause other than those listed above for example, line infection
Prolonged ileus	Absence of bowel function requiring the initiation of nutritional support
Pulmonary embolus	Confirmed radiologically or at autopsy
Deep vein thrombosis	Confirmed radiologically or at autopsy
Limb ischaemia	Compromised circulation in a limb requiring a revascularisation procedure within 30 days of surgery
Major limb amputation	Amputation of a limb due to unsalvageable critical ischaemia within 30 days of surgery
Renal infarction	New renal infarction on post-operative imaging
Renal impairment	Post-operative ≥20% increase in serum creatinine from pre-operative baseline

CPAP – continuous positive airway pressure; IPPV – intermittent positive pressure ventilation.

**Table 3 Tab3:** **Acute kidney injury criteria**

**AKI grade**	**Creatinine criteria**	**Urine output criteria**
1	Rise > 26.4 μmol/L or 150 to 200% of baseline	<0.5 ml/kg/h for >6 h
2	Rise of 200 to 300% of baseline	<0.5 ml/kg/h for >12 h
3	Increase of 300% or creatinine >354 μmol/L with acute rise of at least 44 μmol/L	<0.3 ml/kg/h for >24 h or anuria for 12 h

Legend: Table summarising acute kidney injury criteria.

AKI – acute kidney injury.

### Proposed composite Primary Efficacy Endpoint for Phase 3

The proposed primary efficacy endpoint is a composite Major Adverse Clinical Event (MACE). The selected endpoints represent common, life-threatening complications of major vascular surgery. Ischaemia-reperfusion injury plays a significant role in these events, and thus, it is biologically plausible that RIPC would reduce the frequency of these events. The components are all strictly defined. The occurrence of any of these events in a patient will be classified as a MACE. The occurrence of multiple events in a single patient will also be classified as a single MACE for the purposes of trial analysis. The components of the primary efficacy endpoint are as follows:Cardiovascular deathMyocardial infarctionCerebrovascular accidentRenal failure requiring renal replacement therapyMesenteric ischaemia requiring intervention or biopsy-proven ischaemic colitis

These components of the proposed primary efficacy endpoint have been defined as follows:Cardiovascular death, which is defined as death due to a known cardiovascular cause or where the cause of death is unknown that is, no other cause of death is identified either from the medical history or at post-mortem examination.Myocardial infarction, which will include both perioperative myocardial infarction and myocardial infarction following vascular surgery. It will include silent myocardial infarctions as determined by the trial cardiologist upon examination of trial ECGs and troponin results. The diagnosis of a myocardial infarction will require the presence of at least two of the following:Characteristic ischaemic symptoms lasting at least 20 minutesElectrocardiographic changes including acute ST elevation followed by the appearance of Q waves or the loss of R waves, the development of new left bundle branch block, new persistent T wave inversion lasting at least 24 hours or new ST segment depression persisting over 24 hoursPositive troponin T (>0.1 ng/ml) or troponin I (>0.1 mg/ml) levels with a characteristic rise and fall in levelsNew-onset arrhythmia (ventricular or supraventricular tachycardia or fibrillation) with an associated rise in troponin levelsAlternatively, myocardial infarction will be recorded if the patient develops sudden unexpected cardiac death involving cardiac arrest with symptoms suggestive of myocardial ischaemia and accompanied by presumably new ST elevation or new left bundle branch block and/or fresh thrombus on coronary angiography and/or at post-mortem, but death occurring before blood samples could be obtained or at a time before the appearance of cardiac troponin I or T in the blood.Cerebrovascular accident, which is defined as new onset neurological deficit, accompanied by evidence of cerebral infarction or intra-cerebral haemorrhage on CT scan, or confirmed at autopsy.Renal failure requiring renal replacement therapy, which is defined as the initiation of any form of renal replacement therapy for any reason within 30 days of major vascular surgery.Mesenteric ischaemia requiring intervention or biopsy-proven ischaemic colitis, which is defined as small or large bowel ischaemia at laparotomy or found at autopsy or histologically proven on biopsy.

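### The myocardial infarction definition prints the troponin I cut-off in mg/ml, a million times the troponin T figure beside it, and its 24-hour ECG wording does not fit the single post-operative ECG

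*Protocol article*

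**What the plan says.** The definition stands in the protocol article under *Proposed composite Primary Efficacy Endpoint for Phase 3*. Its decision rule is "The diagnosis of a myocardial infarction will require the presence of at least two of the following". The four criteria are:

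1. ischaemic symptoms;
2. ECG changes, in a list that includes "new persistent T wave inversion lasting at least 24 hours or new ST segment depression persisting over 24" hours, alongside new left bundle branch block and ST elevation followed by Q waves or R-wave loss;
3. positive "troponin T (>0.1 ng/ml) or troponin I (>0.1 mg/ml) levels with a characteristic rise and fall";
4. new-onset "arrhythmia (ventricular or supraventricular tachycardia or fibrillation) with an associated rise in troponin" levels.

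A separate alternative covers sudden cardiac death before troponin could be measured. On silent events the text adds: "It will include silent myocardial infarctions as determined by the trial cardiologist upon examination of trial ECGs and troponin results".

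The measurement schedule is given elsewhere. *Perioperative troponin* specifies "measuring serum high-sensitivity troponin I pre-operatively and at 24, 48 and 72 hours post-operatively", analysed locally at each site. *Perioperative 12-lead electrocardiography* uses the routine pre-operative tracing as baseline and then says: "Every patient will undergo a second 12-lead ECG on the second post-operative day".

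The composite is a listed secondary endpoint (*Secondary endpoints*). Its incidence is to support the phase 3 power calculation (*Aims and objectives*, *Sample size*).

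**The concern.** The protocol describes the components of the composite as strictly defined, but this one cannot be applied as printed. The faulty limb is the operative one, because the trial measures troponin I and not troponin T. Two further parts of the same definition do not sit well with the rest of the protocol: the 24-hour persistence wording against a single post-operative tracing, and a fourth criterion that shares its troponin evidence with the third.

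At stake is the event rate of the composite. One stated purpose of this trial is to replace a 15% figure from 40 pilot patients (0.15 × 40 = 6 patients) with something firmer. The same events also feed the cost and QALY analysis under *Health economics*. If the infarction rule has to be interpreted at adjudication, the resulting rate depends partly on that interpretation. Blinding the cardiologist guards against treating the arms differently. It does not supply the rule.

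**Working it through.** **Unit.** Inputs are the two cut-offs in the troponin criterion. 1 mg = 1,000,000 ng, so 0.1 mg/ml = 0.1 × 1,000,000 = 100,000 ng/ml. The ratio to the troponin T limit is 100,000 / 0.1 = 1,000,000.

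**What remains for a silent infarction.** Number the criteria 1 (symptoms), 2 (ECG), 3 (troponin) and 4 (arrhythmia with troponin rise). Two of four gives six possible pairs. A silent infarction lacks criterion 1, which leaves 2+3, 2+4 and 3+4.

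| Reading of the unit | Pairs open to a silent infarction |
|---|---|
| mg/ml, as printed | 2+4 only |
| ng/ml, as for troponin T | 2+3, 2+4, 3+4 |

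Under the printed unit, even new bundle branch block with a clear troponin rise and fall scores one criterion and does not count, unless an arrhythmia is also present.

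**What one day-2 tracing can show against baseline.** This question is independent of the unit.

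| Named ECG pattern | 24-hour rule? | Shown by one day-2 ECG plus baseline? |
|---|---|---|
| New left bundle branch block | No | Yes |
| ST elevation, then Q waves or R-wave loss | No | Q waves or R-wave loss yes; the preceding ST elevation no |
| T-wave inversion | Yes | Presence yes, duration no |
| ST depression | Yes | Presence yes, duration no |

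The schedule therefore limits part of criterion 2. It does not disable it, and the list opens with a word that makes it non-exhaustive.

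**Overlap of criteria 3 and 4.** Criterion 4 asks for an associated troponin rise but gives no threshold. With the unit corrected, a rise and fall above the cut-off meets criterion 3. The same rise together with a new supraventricular arrhythmia meets criterion 4. The total is two, without symptoms or an ischaemic ECG change, and nothing in the definition says whether that is intended.

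**Stated sample sizes.** The protocol's 0.8, labelled beta, is read as power; two-sided alpha is 0.05. The uncorrected size per arm is n = [1.96√(2p̄(1−p̄)) + 0.842√(p₁(1−p₁) + p₂(1−p₂))]² / (p₁−p₂)², and the continuity-corrected size is (n/4)[1 + √(1 + 4/(n|p₁−p₂|))]².

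- Phase 3, 15% to 10%: n = 686 uncorrected and 726 corrected. The protocol states 726, so it is reproduced.
- This trial, 40% to 25%: n = 152 uncorrected and 165 corrected. The protocol states 166, a difference of one.

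Neither figure uses the infarction cut-off, so neither changes.

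**Sensitivity of phase 3 planning (assumption, not an estimate).** The share of composite events that the wording might lose is unknown. If a share L were lost and the one-third relative reduction held, the control rate would be 15% × (1 − L). The corrected size per arm would be:

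| L | Control rate | n per arm |
|---|---|---|
| 0 | 15% | 726 |
| 10% | 13.5% | 817 |
| 25% | 11.25% | 1,000 |
| 50% | 7.5% | 1,550 |

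This shows only that planning is sensitive to the composite rate. The overlap of criteria 3 and 4 would push the rate the other way.

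**The case against.** The best defence is that the unit is an evident slip. The plausible order of magnitude is printed in the same phrase, and no cardiologist reviewing ECGs and troponin results would apply a limit of 100,000 ng/ml. That is a fair prediction of what will happen, and it rules out forecasting lost events from the unit alone. It does not make the printed threshold usable. A text-extraction fault cannot be excluded, but ng/ml in the same line and μmol/L in Table 3 came through intact.

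A reader might infer that most silent infarctions will go unrecorded. The documents do not support this. They give neither the share of infarctions that are silent nor the mix of ECG patterns, and once the unit is read as ng/ml, ECG change plus troponin is open again. A reader might also infer that the definition demands 24-hour persistence throughout. It does so for two patterns only, and ECGs taken in routine care are not ruled out, although silent infarction is tied to the trial tracings.

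On the overlap, the defence notes that criterion 3 needs a value above the cut-off with a rise and fall, so not every arrhythmia with some troponin release would count twice. That stands. The ambiguity is real, but its frequency is unknown.

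Finally, the composite is secondary here. The primary outcome uses the upper limit of normal or the patient's own baseline value (*Primary efficacy endpoint*) and is untouched. That also stands.

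**Conclusion.** The point holds in three parts of unequal weight.

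- **Unit.** The troponin I cut-off is wrong as written by a factor of 1,000,000 relative to the troponin T figure, in the assay the trial uses. Taken literally, it removes criterion 3 and leaves a silent infarction one route (2+4), apart from the sudden-death alternative. This is the firm part.
- **ECG persistence.** The T-wave and ST-depression patterns require a duration that the single scheduled post-operative ECG cannot establish by itself. Bundle branch block is unaffected, and the list is open.
- **Overlap.** One troponin rise and fall above the cut-off with a new arrhythmia can be read as meeting criteria 3 and 4 together. This is a secondary ambiguity.

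The consequence is confined to a secondary endpoint, the analyses that use its events, and the incidence carried into phase 3 planning. The primary outcome and the stated sample sizes do not change. No number of missed or added infarctions can be derived from the documents, and the sensitivity table should not be read as one.

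**What to change.** Make three wording changes, all before the ECGs and troponins are adjudicated in batches (*Evaluation of perioperative myocardial infarction*):

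1. Correct the troponin I unit, and reconcile the cut-off with the high-sensitivity assays run locally at the sites.
2. Reconcile the 24-hour wording for T-wave inversion and ST depression with the single day-2 ECG. How to do so is for the sponsor and the trial cardiologist to decide; this review proposes no diagnostic rule.
3. State whether one troponin rise may count towards both the troponin and the arrhythmia criterion.

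The first and third cost only an edit to the definition and the adjudication form. The second also costs only wording, unless the sponsor chooses to reconcile the text by changing the ECG schedule. If any cases have already been adjudicated, they should be re-read under the settled wording, with the reader still blinded to allocation.
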